## Abstract

**Background:**

Burkina Faso introduced the Integrated Management of Childhood Illnesses (IMCI) strategy in 2003. However, an evaluation conducted in 2013 found that only 28 % of children were assessed for three danger signs as recommended by IMCI, and only 15 % of children were correctly classified. About 30 % of children were correctly prescribed with an antibiotic for suspected pneumonia or oral rehydration salts (ORS) for diarrhoea, and 40 % were correctly referred. Recent advances in information and communication technologies (ICT) and use of electronic clinical protocols hold the potential to transform healthcare delivery in low-income countries. However, no evidence is available on the effect of ICT on adherence to IMCI. This paper describes the research protocol of a mixed methods study that aims to measure the effect of the Integrated electronic Diagnosis Approach innovation (an electronic IMCI protocol provided to nurses) in two regions of Burkina Faso.

**Methods/design:**

The study combines a stepped-wedge trial, a realistic evaluation and an economic study in order to capture the effect of the innovation after its introduction on the level of adherence, cost and acceptability.

**Discussion:**

The main challenge is to interconnect the three substudies. In integrating outcome, process and cost data, we focus on three key questions: (i) How does the effectiveness and the cost of the intervention vary by type of health worker and type of health centre? (ii) What is the impact of changes in the content, coverage and quality of the IeDA intervention on adherence and cost-effectiveness? (iii) What mechanisms of change (including costs) might explain the relationship between the IeDA intervention and adherence?

**Trial registration:**

Clinicaltrials.gov, NCT02341469.

## Background

Despite a large reduction in under-5 child mortality (from 180 per 1000 live births in 1990 to 83 per 1000 live births in 2015), sub-Saharan Africa failed to reach the Millennium Development Goal 4 target of 60 deaths per 1000 live births [1]. In 1999, the World Health Organization (WHO) developed the Integrated Management of Childhood Illness (IMCI) strategy [2]. This strategy provides an algorithm to guide health workers through a systematic clinical assessment of sick children with the aim of improving the diagnostic classification and the treatment of these children [3–5] and hence reducing mortality [4, 6].

However, effective implementation of IMCI is often constrained by poor adherence to the guidelines [7–9]. Previous studies have reported that adherence to the guidelines decreases over time due to inadequate initial training, shortage of staff and insufficient supervision [10, 11]. Takada et al. [12] have noted that healthcare workers typically find the IMCI chart booklet burdensome and try to work from memory, resulting in a decrease in quality of care. In addition, healthcare workers may omit sections resulting in incomplete assessments [4, 13]. Chaudhary [10] demonstrated that the adherence of health workers improved with supervision. However, regular supervision of health workers after training is often lacking [8, 13], partly due to the lack of resources.

Burkina Faso introduced the IMCI strategy in 2003. However, an evaluation conducted in 2013 found that only 22 % of nurses working in primary care facilities had been trained in IMCI [14]. Only 28 % of children were assessed for three danger signs as recommended by IMCI, and only 15 % of children were correctly classified [14]. About 30 % of children were correctly prescribed with an antibiotic for suspected pneumonia or oral rehydration salts (ORS) for diarrhoea, and 40 % were correctly referred [14].

Recent advances in information and communication technologies (ICT) holds the potential to transform healthcare delivery in low-income countries [15–17]. However, no evidence is available on the effect of ICT on adherence to IMCI. Small-scale studies conducted in Tanzania found ICT to be well accepted by healthcare workers during IMCI consultations [7, 16]. However, the experience with using such technology on a large scale is limited.

In 2010, Terre des Hommes (TdH), a Swiss non-governmental organisation, together with the Ministry of Health (MoH), launched the Integrated electronic Diagnosis Approach (IeDA) intervention with the objective of improving adherence to IMCI guidelines in public primary health centres in two regions of Burkina Faso. In this paper, we present the design of a mixed methods evaluation of this intervention.

Burkina Faso is composed of 13 regions and 63 health districts. The public health system is characterised by a three-tier service structure: (i) at the first level are the districts with 1535 health centres (Centre de Santé et de Promotion Sociale (CSPS)) and the 104 district hospitals (Centre Médical avec Antenne Chirurgicale (CMA)), (ii) at the next level are the nine regional hospitals (Centre Hospitalier Régional (CHR)), and (iii) finally, the third level is comprised of the three national teaching hospitals (Centre Hospitalier Universitaire (CHU)) [18].

The IMCI approach was implemented only at the first level of the pyramid, i.e. in health centres. These facilities deliver a minimum package of services defined by the Ministry of Health comprising both preventive (e.g. vaccinations, antenatal care, health education, and promotion of proper nutrition, hygiene and safe water) and curative measures (e.g. treatment of common illnesses, minor surgery, supply of essential medicine, maternal and child consultations). CSPSs are governed by a management committee (Comite de gestion) composed of members of the community. The district health management team is in charge of supervising CSPSs and analysing routine data collected in them [19].

### The Electronic Register of Consultations and the IeDA intervention

The ‘electronic register of consultations’ or ‘Registre Electronique de Consultations’ (REC) in French was designed in 2010 by TdH [20]. The REC software, based on the CommCare software language, is installed on the open access CommCare platform developed by Dimagi [21]. The REC guides health workers through the IMCI algorithm. By doing so, it aims to improve adherence of nurses to the clinical protocol and to provide the local health district and the MoH with routine data on the management of childhood illnesses. The first versions of the REC were piloted in 2011 and 2012 in 52 primary health facilities located in two districts in the Nord region and perceived by 90 % of users (nurses) as being a supportive tool during consultations [22]. An additional pilot district, Yako, was added in the Boucle du Mouhoun region in 2014 and 2015. Following the pilot phase, the MoH requested TdH to expand the implementation of the REC to the remaining health districts of both regions.

In order to do so, TdH launched in 2014 the IeDA intervention, which includes the following five components, delivered at district and health centre levels:Development and implementation of the improved versions of the REC in all primary facilities of the two regions (district level).Provision, with the Ministry of Health, of a 7-day training course on IMCI guidelines including 2 days on the use of the REC to all primary health workers working in each district to be covered (district level).Development of a quality assurance mechanism through which each district and health centre is encouraged to find appropriate solutions in response to their local needs (district and health centre levels).Supervise every month every health centre benefiting from the intervention and support health district authorities in their annual supervision of health centres (health centre level).Development of a health information system based on the data collected through the REC and fed back to the district managers and heads of health centres (district and health centre levels).

## Methods/design

### The evaluation methods

The IeDA intervention is being evaluated using a mixed methods study design composed of the following three interlinked studies (see Fig. 1):

**Fig. 1 Fig1:**
[figure not shown]
Evaluation mixed methods study framework

A stepped-wedge trial to evaluate the effect of IeDA on the adherence to IMCI guidelines in primary health facilitiesA cost-effectiveness analysis (CEA) to assess the value for money of the delivery of IeDAA realistic evaluation to understand the implementation process, the mechanisms by which the IeDA intervention leads to change and to identify factors that may affect these mechanisms at the health centre and community levels

These three studies are taking place in a total of eight health districts across the Nord and Boucle du Mouhoun regions, with the three districts where TdH piloted the REC excluded from the evaluation.

### The stepped-wedge trial

Stepped-wedge trials are a type of cluster randomised trial in which clusters receive the intervention at different time points and the order in which they receive the intervention is randomised [23, 24]. Some aspects of the intervention can only be delivered at the district level, and other aspects are most conveniently delivered by district and so, we are using a cluster randomised trial with districts as clusters. The two regions have 11 districts, three of which received the pilot intervention and so, the evaluation will be restricted to the eight remaining districts. The implementing agencies (the MoH and TdH) need to roll out the intervention in a phased implementation approach for logistical reasons, with the intervention introduced into one additional district every 4 months. Hence, we are using a stepped-wedge design, with the order in which the eight districts receive the intervention determined by computer-based, restricted randomisation (Fig. 2).

**Fig. 2 Fig2:**
[figure not shown]
The sequence of districts receiving the intervention after each period of 4 months during the stepped-wedge trial

The intention was that the intervention would eventually be delivered to all primary health centres in all eight districts. Also, during the period preceding the intervention (i.e. in year 1 step 1), a first round of data collection would be conducted in the eight districts to provide pre-intervention measurements in all districts.

The aim of the trial is to determine whether the IeDA intervention increases adherence to the IMCI algorithm and hence improves classification, referral, prescription and counselling during under-5 child consultations in health centres. This will be determined by observation of child consultations followed by a repeat consultation by study staff in selected CSPS.

There are two co-primary outcomes, one task-based and one results-based, both measured at individual level using direct observation [25–27]:Degree of adherence to IMCI guidelines, measured as a quantitative variableCorrect disease classification and prescription, measured as a binary variable

The secondary outcomes related to under-5 children consultations are as follows:Correct identification of danger signsCorrect classification of childrenPrescription of the correct medicineCorrect referral or hospitalisationCorrect counselling delivered to child carer

### Selection of primary health centres

The evaluation is being conducted in ten randomly chosen primary health centres per health district. The list of CSPSs selected for the evaluation has not been communicated to the implementing agency to reduce the likelihood that they target these health centres for more intensive support. Ten CSPS per district was chosen to give sufficient contextual variation, while minimising logistical difficulties and ensuring that some CSPS in each district were not selected to allow for selection concealment. Only primary health centres with staff trained in IMCI were considered for selection, and all hospitals were excluded. The intervention effect may vary by health centre workload, and so, the selection was stratified on the 2013 annual under-5 consultations caseload, as provided by the MoH. For the 337 CSPSs with staff trained in IMCI in the eight districts under evaluation, the annual caseload was transformed into a daily rate by dividing it by 261 days (i.e. the number of working days). Out of the 337 CSPSs, 13 were excluded, either because of missing caseload data (six CSPS) or because of a zero recorded caseload (seven CSPS). Out of the remaining 324 CSPSs, a further 54 CSPSs were excluded because they had caseloads of less than three cases per working day, which would have limited the number of consultations that could be observed in these facilities. Although these 54 CSPSs represented 17 % of the remaining 324 CSPSs, they only represent 4 % of the total caseload in 2013. In each district, five CSPSs were then randomly selected among those with fewer than seven cases per working day and five CSPSs were randomly selected among those with seven cases or more per working day (on average). Seven cases were chosen for the cutoff as this ensured there were at least nine CSPSs in each of the two strata in each district. Data will be collected in the same ten CSPSs per district during each step of the stepped-wedge trial during a 1- to 2-day visit (see the ‘Data collection’ section below).

#### Sample size calculation

Using the method described by Hussey and Hughes [28] and assuming that:Ten health centres in eight districts will be visited every step.A harmonic mean of ten children will present at each health facility over the course of a 1- to 2-day visit.Sampling ten children per facility per round carries a design effect of 2.The coefficient of variation between clusters is 0.3.

Then, there is 90 % power to detect an increase in the correct diagnosis and treatment from 25 to 33 %. If there is only a harmonic mean of four children at each health centre, there will be 98 % power to show an increase from 25 to 40 %.

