#### Analysis

The stepped-wedge design can be analysed in different ways [31]. In the primary analysis, each step will be analysed using methods appropriate for a parallel cluster randomised trial, using district-level summaries of the outcome to calculate a difference measure. These difference measures will be combined across steps using inverse variance weighting. Hypothesis testing will be based on bootstrapping or a permutation test.

In the secondary analysis, the method described by Hussey and Hughes [28] will be used. As the outcome is likely to be relatively common, the risk difference will be modelled using generalised estimating equations at the level of the child consultation, with fixed effects for intervention versus control phase, time step and district and clustering at the level of the health centre.

Potential imbalances at the level of the child and the health centre between intervention and control phases will be investigated and any imbalances will be adjusted for. A priori, adjustment will also be made for district-level summaries of the outcome at baseline.

A detailed statistical analysis plan will be prepared before the end of data collection.

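### The stated 90 % and 98 % power belong to the secondary Hussey and Hughes analysis; the planned primary analysis has less power on the same inputs

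*Protocol article*

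**What the plan says.** The Sample size calculation section opens "Using the method described by Hussey and Hughes [28] and assuming that" and lists its inputs: "Ten health centres in eight districts will be visited every step"; "A harmonic mean of ten children will present at each health facility" over a visit; a design effect of 2 for ten children per facility per round; and a between-cluster coefficient of variation (CV) of 0.3. It concludes that there is 90 % "power to detect an increase in the correct diagnosis and treatment from 25 to 33" %. With a harmonic mean of four children it gives 98 % "power to show an increase from 25 to 40" %.

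The Analysis section then separates two analyses. "In the primary analysis, each step will be analysed using methods appropriate for a parallel cluster randomised trial", using district-level summaries. The step-specific differences are pooled with inverse-variance weights and tested by bootstrap or permutation. Next: "In the secondary analysis, the method described by Hussey and Hughes [28] will be used". Adjustment for district baseline summaries is fixed a priori. No power is given for the primary analysis.

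**The concern.** The two methods use different information. The Hussey and Hughes model combines comparisons between districts with before-and-after comparisons inside each district, so much of the between-district variation cancels. The primary analysis compares treated with untreated districts inside one step at a time (1 v 7, 2 v 6, up to 7 v 1). The final step, when all eight districts are treated, contributes nothing, and the pre-intervention round enters only as a baseline adjustment. Between-district variation therefore stays in the primary contrast, except for the part that baseline adjustment removes.

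A reader will take 90 % as the power of the primary test on the binary co-primary outcome. If the true figure is well below that, a null primary result could be over-read as evidence against an 8-point gain.

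**Working it through.** **Inputs from the article.** There are 8 districts with one crossing over per period. The pre-intervention round plus eight periods is read as T = 9 rounds. There are 10 centres × 10 children = 100 per district-round, the design effect is 2, the control proportion is 0.25 and the CV is 0.3.

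**Assumptions not in the article.** Two-sided alpha 0.05, normal approximation, a district effect constant over time, an immediate and constant intervention effect, and independent residuals between rounds (relaxed in step 4).

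- σ² = 0.25 × 0.75 × 2/100 = 0.00375 (ten children), or 0.25 × 0.75 × 2/40 = 0.009375 (four children).
- τ = 0.3 × 0.25 = 0.075, so τ² = 0.005625.

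**1. Reproduce the stated figures (Hussey and Hughes).**

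Variance = Iσ²(σ² + Tτ²) / [(IU − W)σ² + (U² + ITU − TW − IV)τ²], with I = 8, U = 36, W = V = 204. Then IU − W = 84, and U² + ITU − TW − IV = 1296 + 2592 − 1836 − 1632 = 420.

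- Ten children: 0.00163125 / (0.315 + 2.3625) = 0.000609; SE 0.0247; 0.08/SE = 3.24; power 0.900 (stated 90 %).
- Four children: 0.0045 / (0.7875 + 2.3625) = 0.001429; SE 0.0378; 0.15/SE = 3.97; power 0.978 (stated 98 %).

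Both figures reproduce. With 8 rounds instead of 9 the first would be 87.4 %.

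**2. Variance of the primary within-step estimator.**

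At step k (k = 1 to 7) there are k treated and 8 − k untreated districts. The inverse-variance weight is proportional to k(8 − k)/8, that is 0.875, 1.5, 1.875, 2, 1.875, 1.5, 0.875, with sum 10.5. The district in position p of the order gets total weight (4.5 − p)/10.5 across steps. Hence

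Variance = Aτ*² + Bσ², with A = 2(3.5² + 2.5² + 1.5² + 0.5²)/10.5² = 42/110.25 = 0.381 and B = 1/10.5 = 0.0952.

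Here τ*² is the persistent between-district variance left after baseline adjustment: τ² with no adjustment, σ² for change from baseline, and τ²σ²/(τ² + σ²) for the ideal adjustment with a known slope.

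**3. Results with independent rounds (closed form).**

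| Adjustment | 25 v 33 %, ten children | 25 v 40 %, four children |
|---|---|---|
| None (not planned) | SE 0.0500, power 36 % | SE 0.0551, power 78 % |
| Change from baseline | SE 0.0423, power 47 % | SE 0.0668, power 61 % |
| Known slope (ceiling) | SE 0.0348, power 63 % | SE 0.0472, power 89 % |

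Permutation simulations agree. For 25 v 33 % they give 39 % unadjusted, 49 to 52 % for change from baseline, 62 to 63 % with the slope known, 52 to 56 % with the slope estimated at each step, and 48 % if the weights are estimated too. For 25 v 40 % with four children, adjusting with an estimated slope gives 82 %, or 70 % with estimated weights. These runs permuted the district order freely. Restricting to the 4224 allowed orders gave much the same (38 % unadjusted, 49 % change from baseline, 54 to 63 % with baseline as covariate).

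**4. Persistent centre differences.**

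The same ten centres are revisited. A design effect of 2 with ten children implies an intra-centre correlation of (2 − 1)/(10 − 1) = 1/9. The between-centre part of σ² is then 0.1875/(9 × 10) = 0.00208. If all of it persists, σ² falls to 0.00375 − 0.00208 = 0.00167 and τ² rises to 0.00771.

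- Change from baseline: variance 0.476 × 0.00167 = 0.000794; SE 0.0282; power 81 %.
- Known slope: variance 0.381 × 0.00137 + 0.0952 × 0.00167 = 0.000681; SE 0.0261; power 86.6 %.

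Simulation gives 79 % with the slope estimated at each step and 82 % for change from baseline. With half the centre variance persisting it gives 66 % and 61 %. Hussey and Hughes power also rises, to about 97 % (half) and above 99 % (full), so the gap does not close.

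**The case against.** The article says openly which method produced its power figures, and they are correct for that method. A reader might infer an arithmetic error; there is none.

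A reader might also infer that the primary test has under 40 % power. That is the unadjusted analysis, which the protocol rules out by fixing baseline adjustment in advance. District is already a fixed effect in the secondary model, so the adjustment matters chiefly for the primary one. The 36 to 39 % is a lower bound for an analysis that is not planned.

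Nor can 63 % be called the most that the primary analysis can reach. That ceiling treats each round's residual as fresh noise, which fits poorly with repeat visits to the same centres. The article does not say how much centre variation persists.

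The primary analysis is also not fixed closely enough for one power value: the difference measure, the variance estimator and the choice of bootstrap or permutation are open, and details may properly sit in the analysis plan. The four-child scenario carries a design effect stated only for ten. With an intra-centre correlation of 1/9 it would be 1 + 3/9 = 1.33, and primary power would be about 79 % (change from baseline) to 95 % (known slope). Yet the stated 98 % matches a design effect of 2; with 1.33 the Hussey and Hughes figure would be 99.8 %.

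All of this limits the size of the shortfall. None of it makes the stated power that of the primary analysis.

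**Conclusion.** The point holds as a mismatch between the power calculation and the named primary analysis. On the protocol's inputs, with independent rounds and two-sided alpha 0.05, the baseline-adjusted primary analysis has about 50 to 63 % power for 25 v 33 %, against the stated 90 %. For 25 v 40 % with four children and a design effect of 2 it has about 60 to 89 %, against 98 %. Full persistence of centre differences could lift the 25 v 33 % figure to roughly 80 to 86 %, still short of 90 %.

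The size depends mainly on the CV. At 0.1, within-step power would be about 88 to 92 %; at 0.2, about 60 to 75 %. The protocol states 0.3. The documents do not support a single replacement value such as 60 %. No estimate, test or error rate is affected; what is wrong is the assurance a reader takes from the power statement.

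**What to change.** State in the Sample size calculation section that 90 % and 98 % apply to the secondary Hussey and Hughes analysis. Add simulated power for the primary within-step permutation test with baseline adjustment, over the allowed allocations. Report it as a range, with the assumptions stated: how baseline is adjusted for, whether slope and weights are estimated, how much between-centre variation persists across visits, the design effect used for four children, and alpha. Do not insert a single figure.

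The cost is a few sentences and a short simulation. No further data are needed and the design is unchanged; the published power becomes less favourable.

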#### Randomisation

There are eight districts (five in Boucle du Mouhoun region and three in the Nord region) in the stepped-wedge trial. Restricted randomisation was used to allocate one cluster (i.e. one district) to receive the intervention in each of the eight time periods [29]. The order in which the eight districts receive the intervention was subject to three constraints that address the following circumstances in which the trial was being performed:An international organisation will be implementing a performance-based financing (PBF) intervention in four of the eight districts during the study, which may influence the performance of the health workers. In addition, two of the eight districts will act as ‘control’ clusters for their study, and so, it would be better if the IeDA intervention does not start in both these clusters before starting in any other cluster.An international donor is prepared to provide support for two of the five districts in the Boucle du Mouhoun region, but they needed to start doing this soon.There needs to be some balance in the randomisation order across the two regions.

Hence, the following restrictions were applied:There must be one PBF intervention district and one PBF non-intervention district (either a control district or one excluded from the study) in each pair of randomised districts, i.e. in the first and second districts to receive the intervention, the third and fourth districts, the fifth and sixth districts and the seventh and eight districts. The difference in the average order of the PBF intervention districts and the non-intervention districts must be less than one. The first three districts must not include both PBF control districts.At least one of the first two districts must be in the Boucle du Mouhoun region.At least one of the first three districts and at least one of the last three districts must be from the Nord region.

